**8.3. Discontinuations**

***8.3.1. Discontinuation of Patients***

The criteria for enrollment must be followed explicitly. If a patient who does not meet enrollment criteria is inadvertently enrolled, that patient should be discontinued from the study, and Lilly or its designee must be contacted.

In addition, patients will be discontinued from the study drug and from the study in the following circumstances:

• Enrollment in any other clinical trial involving an off-label use of an investigational drug or device or enrollment in any other type of medical research judged not to be scientifically or medically compatible with this study.

• If Exclusion Criterion [11-32] is observed, or develops, after entry or enrollment. In this case, the patient will be discontinued from the study at the next visit or sooner in the event of a safety exclusion criterion.

• The investigator decides that the patient should be withdrawn. If this decision is made because of a serious adverse event or a clinically significant laboratory value, the study drug is to be discontinued and appropriate measures are to be taken. Lilly or its designee is to be alerted immediately. Refer to Section 10.3, Safety Evaluations.

• The patient or attending physician requests that the patient be withdrawn from the study.

• The patient, for any reason, requires treatment with another therapeutic agent that has been demonstrated to be effective for treatment of the study indication. In this case, discontinuation from the study occurs prior to

introduction of the new agent.

• The investigator or Lilly, for any reason, stops the study or stops the patient's participation in the study.

Patients who discontinue the study early will have end-of-study procedures performed as shown in the Study Schedule (Protocol Attachment LYDZ(b).1).

***8.3.2. Discontinuation of Study Sites***

Study site participation may be discontinued if Lilly, the investigator, or the ethical review board of the study site judges it necessary for any reason.

***8.3.3. Discontinuation of the Study***

The study will be discontinued if Lilly judges it necessary for any reason.

**9. Treatment**

**9.1. Treatments Administered**

***9.1.1. Study Period II***

This study involves a comparison of atomoxetine 40-100 mg/day administered orally, twice daily (BID) with placebo. Patients who meet all screening criteria will be dispensed blinded medication and instructed to begin doses the morning following Visit

2. Patients will be randomized 1:1 to either atomoxetine or placebo some time between Visit 2 and 4. Since the time at which randomization occurs is double-blinded, neither the investigator nor the patient will know when randomization occurs. Further, because of the potential for a double-blind placebo lead-in, any patients randomly assigned to atomoxetine may receive placebo some time during the potential lead-in phase. Thus,

patients in the atomoxetine group may receive atomoxetine as early as Visit 2 or as late as

Visit 4. The study drug is to be taken by the patient twice-daily, once in the morning and once in the afternoon or early evening. It is strongly recommended to take the study medication with food.

Patients randomized to atomoxetine will:

• begin treatment with atomoxetine 40 mg/day dosed BID for a minimum of 7 days; then,

• the patient will receive atomoxetine 80 mg/day dosed BID for a minimum of 7 days.

Following Visit 3, one unscheduled dose decrease is allowed if needed for tolerability or safety. Only one dose decrease will be permitted during Study Period II.

Starting at Visit 5, if in the judgment of the investigator, the patient has significant residual symptoms, the dose can be increased to the maximum dose of 100 mg/day (dosed 50 mg BID). However, patients who previously required a dose decrease due to safety or tolerability will not be permitted to have a dose increase.

The unscheduled dose decrease or dose increase will only be allowed by one dose level (that is, 80 mg/day to 40 mg/day, 100 mg/day to 80 mg/day, or 80 mg/day to 100 mg/day). Patients unable to tolerate 40 mg/day (dosed 20 mg BID) should be discontinued.

The investigator or his/her designee is responsible for explaining the correct use of the investigational agent(s) to the patient, verifying that instructions are followed properly, maintaining accurate records of study drug dispensing and collection, and returning all unused medication to Lilly or its designee at the end of the study.

Patients will be instructed to contact the investigator as soon as possible if he or she has a complaint or problem with the study drug so that the situation can be assessed.

***9.1.2. Study Period III***

All eligible patients who complete the double-blind Study Period II will have the option

of participating in a 12-week open-label extension period. In Study Period III, study drug

(atomoxetine) will be dispensed to all patients.

Dosing of atomoxetine during the open-label period will commence the morning immediately following the last dose of blinded medication. Dosing may be once daily or twice-daily administration. It is strongly recommended to take the study medication with food.

The starting dose of atomoxetine will be initiated at 7 days of 40 mg/day followed by 7 days of 80 mg/day for those dosed once daily. For those patients prescribed BID dosing in the open-label period, 18 mg capsules were chosen for the lowest starting dose as 20 mg capsules are not available in the marketed form of atomoxetine.

After the initial titration period, the dose may be titrated freely (that is, the dose may be increased or decreased at any time) between 36 mg/day and 100 mg/day during the remainder of Study Period III depending on the patient’s clinical response.

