the investigator nor the patient will know when randomization occurs. Further, because of the potential for a double-blind placebo lead-in, any patient randomly assigned to atomoxetine may receive placebo some time during the potential lead-in phase. Patients in the atomoxetine group may receive atomoxetine as early as Visit 2 or as late as Visit 4. The study drug is to be taken by the patient twice-daily, once in the morning and once in the afternoon or early evening. It is strongly recommended to take the study medication with food. Patients randomized to atomoxetine will begin treatment with 40 mg/day (dosed 20 mg twice daily [BID]) for a minimum of 7 days. Immediately following the last dose of 40 mg/day (dosed 20 mg BID), the patient will receive 80 mg/day (dosed 40 mg BID) atomoxetine for a minimum of 7 days. Following Visit 3, one unscheduled

dose decrease is allowed if needed for tolerability or safety. Only one dose decrease will

be permitted during Study Period II.

Starting at Visit 5, if in the judgment of the investigator, the patient has significant residual symptoms, the dose can be increased to the maximum dose of 100 mg/day (dosed 50 mg BID). However, patients who previously required a dose decrease due to safety or tolerability will not be permitted to have a dose increase.

The unscheduled dose decrease or dose increase will only be allowed by one dose level (that is, 80 mg/day to 40 mg/day, 100 mg/day to 80 mg/day, or 80 mg/day to 100 mg/day). Patients unable to tolerate 40 mg/day (dosed 20 mg BID) should be discontinued. Efficacy data and health outcome measures as outlined in the schedule of events will be evaluated.

If the patient has access to the internet, the patient-rated scales (electronic patient- reported outcomes [e-PROS]) may be completed by the patient outside of the investigator’s office. The patient will be permitted to log into the study website 3 days prior to the originally scheduled visit to begin completing patient-rated questionnaires. The patient may log in and out of the study website without losing any data captured at

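### Section 9.1.2 puts every once-daily extension patient on 80 mg/day in the second week, including those lowered from that dose for safety or tolerability in Study Period II

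*Protocol*

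**What the plan says.** **Study Period II.** After the starting dose of 20 mg twice daily, Section 7.1 states that "the patient will receive 80 mg/day (dosed 40 mg BID) atomoxetine". One decrease for tolerability or safety is allowed after Visit 3. Section 9.1.1 limits its size: "The unscheduled dose decrease or dose increase will only be allowed by one dose level (that is, 80 mg/day to 40 mg/day", with the steps between 80 and 100 mg/day listed after it. A patient lowered to 40 mg/day stays in the study, since the stopping rule applies one level further down: "Patients unable to tolerate 40 mg/day (dosed 20 mg BID) should be discontinued". From Visit 5 the dose may be raised for residual symptoms, but "patients who previously required a dose decrease due to safety or tolerability will not be permitted to have a dose increase".

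**Study Period III.** Section 7.1 makes completers of Study Period II eligible for the extension, with no restriction by dose history. Section 9.1.2 says "Dosing may be once daily or twice-daily administration". For once-daily patients the starting dose is to be "initiated at 7 days of 40 mg/day followed by 7 days of 80 mg/day for those dosed once daily". For twice-daily patients, "18 mg capsules were chosen for the lowest starting dose", and no 80 mg/day step is given. Then: "After the initial titration period, the dose may be titrated freely", within 36 to 100 mg/day.

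**The concern.** The protocol foresees patients who need to come down from 80 to 40 mg/day, retains them, and protects them from re-escalation for the rest of the double-blind period. In the extension that protection lapses. On the plain wording of Section 9.1.2, a once-daily patient goes back to 80 mg/day after one week, and holding at 40 mg/day in the second week would depart from the written schedule. The investigator is then left with choosing twice-daily dosing from the start, departing from the schedule, or withdrawing a patient who may do well at 40 mg/day, a dose inside the protocol's own range.

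This is not a contradiction, because the bar on increases is written for Study Period II only. What is at stake is short-term open-label tolerability in a foreseeable subgroup. The Visit 6 comparison is complete before the extension starts.

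**Working it through.** The plan gives no figure on this point to reproduce. The check is a reading of the dosing rules together with some day and dose counts.

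**Is there an exception anywhere?** The extension dosing text is in the Synopsis, Sections 7.1, 7.2, 9.1.2, 9.2, 9.4 and 9.5.1. None exempts patients with an earlier decrease, directs them to twice-daily dosing, or carries the no-increase rule forward. Section 8.3.1 covers discontinuation only.

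**When does the step fall?** Extension day 1 is the day after Visit 6 (Section 7.1).
- Days 1–7: 40 mg/day. Days 8–14: 80 mg/day. Free titration from day 15.
- Extension length from the Study Schedule: 2 + 5 + 5 = 12 weeks = 84 days. Share at the fixed 80 mg/day step: 7 / 84 = 8.3%.
- Visit 7 is 10 to 18 days after Visit 6 (target 14). By day 10 the patient has had days 8, 9 and 10 of the step, which is 3 days; by day 14 or day 18, all 7. The first scheduled visit therefore follows 3 to 7 days of the step.

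**How do the single doses compare?** In Study Period II, 80 mg/day was 40 mg twice daily and 40 mg/day was 20 mg twice daily.
- 80 mg once daily against the single dose before the decrease: 80 / 40 = 2.
- 80 mg once daily against the single dose after the decrease: 80 / 20 = 4.

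These ratios compare dose sizes and do not measure risk. Section 9.4 reports that doses up to 100 mg/day have been studied both single and divided with no serious safety concern.

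**Does a recorded decrease show intolerance of 80 mg/day?** Not always.
- Target visit times: Visit 3 = week 2; Visit 4 = 2 + 3 = week 5; Visit 5 = 5 + 3 = week 8; Visit 6 = 8 + 4 = week 12.
- Decreases are allowed from week 2, but active drug may start as late as Visit 4 (Section 9.3). Assuming the 7-day minimum at 40 mg/day, 80 mg/day may be first reached only at week 5 + 1 = week 6.
- Some decreases in the atomoxetine arm can therefore precede 80 mg/day, and decreases in the placebo arm say nothing about atomoxetine.

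**What would the twice-daily route give?** 2 × 18 = 36 mg/day, close to the 2 × 20 = 40 mg/day on which such a patient finished Study Period II.

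**How many patients?** This cannot be estimated. The protocol gives no rate of 80-to-40 mg/day decreases, of entry to the extension, or of once-daily choice.

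**The case against.** The strongest reply is that this is a defensible uniform schedule. Former placebo and former atomoxetine patients get the same open-label re-titration, which makes sense when decreases were made blind. A prescriber who knows of the decrease can choose twice-daily dosing and avoid the step, or withdraw the patient. Section 9.4 reports no serious safety concern with single or divided doses up to 100 mg/day. Section 10.3.1 foresees dose reductions for adverse events. Some patients may also tolerate 80 mg/day at a second attempt after a week at 40 mg/day.

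Much of this stands as a limit on size. The twice-daily route is real, some decreases are weak evidence of intolerance, and the step is short. It does not supply the missing exception, however:

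- Section 9.1.2 leaves dosing frequency open and does not link it to dose history.
- Withdrawal ends participation for someone who may tolerate 40 mg/day.
- Section 9.4 speaks of serious safety in general, not of patients already lowered for tolerability.
- Section 10.3.1 is a reporting rule, not a dosing permission.
- Exclusion criterion 14 mentions intolerable side effects on atomoxetine, but using it to remove these patients would defeat Section 9.1.1, which keeps them in.

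**Conclusion.** The point holds and is minor. As written, Section 9.1.2 returns once-daily patients with an earlier 80-to-40 mg/day decrease to 80 mg/day on extension days 8–14 and gives the investigator no stated discretion to hold the dose. The effect is confined to 7 of 84 days of an optional open-label period, in a subgroup of unknown size, and only to patients for whom once-daily dosing is chosen. Only those on atomoxetine when the decrease was made return to a dose that may have caused trouble. Neither the primary analysis nor any other randomized comparison is affected. The conclusion rests on reading the once-daily schedule as mandatory, which its wording supports, and on there being no dosing instruction outside this protocol that supplies the exception.

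**What to change.** Add one sentence to Section 9.1.2 after the once-daily schedule:

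*Patients whose dose was decreased from 80 to 40 mg/day for safety or tolerability in Study Period II may remain at 36–40 mg/day instead of increasing to 80 mg/day, at the investigator's discretion.*

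The schedule stays the default for all other once-daily patients. No new supplies are needed: 40 mg/day is one 40-mg capsule and 36 mg/day is two 18-mg capsules, both listed for Study Period III in Section 9.2. The 36–100 mg/day range is unchanged. The rule uses the decrease recorded under blind, so nobody is unblinded.

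The cost is that some former placebo patients may stay at a low dose a little longer, while Section 9.4 suggests most adults need more than 60 mg/day. The permission adds at most the 7 days before free titration opens on day 15.

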**9.2. Materials and Supplies**

**Table LYDZ(b).1. Clinical Study Materials Informationa**

**Test Material Source Dose Strength Packaging**

**Study Period II** Atomoxetine hydrochloride

Eli Lilly and Co. Indianapolis, IN

20 mg

25 mg

40 mg

Capsules in blister cards, blister packs,

or bottles

Placebo Eli Lilly and Co.

Indianapolis, IN

N/A Capsules in blister cards, blister packs,

or bottles

**Study Period III**

Atomoxetine hydrochloride

Eli Lilly and Co. Indianapolis, IN

18 mg

40 mg

60 mg

Market Image

Bottles

**a** All study materials should be stored at room temperature.

Study drug will be labeled in accordance with Lilly Standard Operating Procedures and the applicable guidelines and regulations of the United States of America where the study is to be conducted. Proper measures will be taken to ensure atomoxetine and placebo capsules are indistinguishable.

The investigator or his/her designee is responsible for explaining the correct use of the investigational agent(s) to the patient, verifying that instructions are followed properly, maintaining accurate records of study drug dispensing and collection, and returning all unused medication to Lilly or its designee at the end of the study.

Patients will be instructed to contact the investigator as soon as possible if he or she has a complaint or problem with the study drug so that the situation can be assessed.

**9.3. Method of Assignment to Treatment**

Patients who meet all criteria for enrollment will be randomized 1:1 to double-blind treatment sometime between Visit 2 and Visit 4. However, because of the potential for a double-blind placebo lead-in and because any patients randomly assigned to atomoxetine may receive placebo some time during the potential lead-in phase, patients in the atomoxetine group may receive atomoxetine as early as Visit 2 or as late as Visit 4. During the double-blind treatment period of the study (Study Period II) assignment to treatment groups will be determined by a computer-generated random sequence using an interactive voice response system (IVRS). The IVRS will be used to assign packages containing double-blind study drug to each patient.

During the open-label extension period of the study (Study Period III) market-image atomoxetine will be supplied by Lilly.

To achieve between group comparability for site factors, patients will be randomized at the site level.

**9.4. Rationale for Selection of Doses in the Study**

The atomoxetine dose of 40 mg/day to 100 mg/day in the double-blinded period of the study is based on previous data from ADHD trials. Results of clinical studies of atomoxetine in adults with ADHD suggest that most patients require doses >60 mg/day, and that many adults require doses up to 100 mg/day. Doses of atomoxetine up to 100 mg/day have been studied as both single and divided doses without evidence of any serious safety concerns. The maximum dose to be administered in this study is 100 mg/day for any patient regardless of weight.

For patients prescribed BID dosing in the open-label extension period, 18 mg capsules were chosen for the lowest starting dose as 20 mg capsules are not available in the marketed form of atomoxetine.

**9.5. Selection and Timing of Doses**

The dose of atomoxetine was selected based on experience in several clinical trials in children, adolescents, and adults. Atomoxetine has been shown to be efficacious for ADHD at doses up to 100 mg/day, and has been efficacious whether the total daily dose

is given once daily or divided into two separate doses. The regimen of twice-daily dosing

was chosen because data from B4Z-US-LYBM (a study in adults with ADHD that compared BID dosing to QD dosing) showed a small, but significant advantage in treating the symptoms of ADHD when dosing was administered BID (B4Z-US-LYBM, data on file, Eli Lilly & Company). The atomoxetine doses in this study are consistent with the FDA label recommendations for the treatment of ADHD.

***9.5.1. Special Treatment Considerations***

Atomoxetine is to be taken twice-daily during the double-blind phase (Study Period II). The first dose should be taken in the morning and the second dose should be taken in the afternoon or early evening. Atomoxetine may be taken once daily or twice daily during the extension phase (Study Period III). Atomoxetine should be swallowed whole; the capsules should not be crushed, broken or opened. Atomoxetine is satisfactorily absorbed regardless of whether it is taken with or without food. It has been shown to be equally effective if the patient has eaten prior to taking the medication or not. However, some data suggest that tolerability is better when atomoxetine is administered with food. Therefore, it is strongly recommended to take the study medication with food.

**9.6. Blinding**

Study Period II is the double-blind phase of the study.

To preserve the blinding of the study, a minimum number of Lilly personnel will see the randomization table and treatment assignments before the study is complete.

Emergency unblinding for adverse events may be performed through an IVRS, which may supplement or take the place of emergency codes generated by a computer drug- labeling system. This option may be used ONLY if the patient's well-being requires knowledge of the patient’s treatment assignment. All calls resulting in an unblinding event are recorded and reported by the IVRS. All codes, whether sealed or opened, must be returned to Lilly upon completion of the study.

The investigator should make every effort to contact the Lilly clinical research physician prior to unblinding a patient's treatment assignment. If a patient's treatment assignment is unblinded, Lilly must be notified immediately by telephone.

If an investigator, site personnel performing assessments, or patient is unblinded, the patient must be discontinued from the study. In cases where there are ethical reasons to have the patient remain in the study, the investigator must obtain specific approval from a Lilly clinical research physician for the patient to continue in the study.

**9.7. Concomitant Therapy**

In general, concomitant medications with primarily central nervous system (CNS)

activity are not allowed in this protocol.

Protocol Attachment LYDZ(b).3 lists commonly used drugs, which may or may not be used acutely or for longer periods during Study Period II and Study Period III. All concomitant medications will be recorded on electronic case report forms (e-CRFs), including dose and duration of treatment.

Any changes to this list will be communicated to investigators and will not constitute a protocol amendment. **Patients must sign the informed consent document before stopping any excluded medications, if the reason they are stopping the excluded medications is for the sole purpose of being allowed to enter the study.**

Patients requiring excluded concomitant drugs will be discontinued from the study, unless approval has been obtained from the Lilly physician monitor or Lilly’s designated representative.

Patients are not allowed to take medications for sedation or sleep during the study.

**9.8. Treatment Compliance**

Patient compliance with study medication will be assessed at each visit. Compliance will be assessed by direct questioning and counting returned capsules.

Patients who are significantly noncompliant will be discontinued from the study. A patient will be considered *compliant* during a visit interval if he or she took the prescribed medication at the prescribed dose on at least 75% of the days in the visit interval. Similarly, a patient will be considered significantly *noncompliant* if he or she intentionally or repeatedly takes less than the prescribed amount (75%) of medication or more than the prescribed amount (120%) as judged by the investigator.

If a patient is not compliant during a visit interval, the patient will be counseled regarding the importance of compliance in this study. The patient may be discontinued at this time if, in the opinion of the investigator, the patient is deemed unlikely to become compliant.

The second time that a patient is noncompliant with his or her dosage schedule; he or she must be discontinued from the study unless noncompliance results from unforeseen circumstances (that is, blizzard, illness). In such instances, the Lilly research physician who is responsible for monitoring the study may grant permission for the patient to remain in the study.

